# A randomized wait-list control trial to evaluate the impact of a mobile application to improve self-management of individuals with type 2 diabetes: a study protocol

**DOI:** 10.1186/s12911-016-0381-5

**Published:** 2016-11-15

**Keywords:** E-Health, Randomized controlled trial, Diabetes, Self-management, Implementation science, Mobile health

## Abstract

**Background:**

Management of diabetes through improved glycemic control and risk factor modification can help prevent long-term complications. Much diabetes management is self-management, in which healthcare providers play a supporting role. Well-designed e-Health solutions targeting behavior change can improve a range of measures, including glycemic control, perceived health, and a reduction in hospitalizations.

**Methods:**

The primary objective of this study is to evaluate if a mobile application designed to improve self-management among patients with type 2 diabetes (T2DM) improves glycemic control compared to usual care. The secondary objectives are to determine the effects on patient experience and health system costs; evaluate how and why the intervention worked as observed; and gain insight into considerations for system-wide scale-up. This pragmatic, randomized, wait-list-control trial will recruit adult participants from three Diabetes Education Programs in Ontario, Canada. The primary outcome is glycemic control (measured by HbA1c). Secondary outcomes include patient-reported outcomes and patient-reported experience measures, health system utilization, and intervention usability. The primary outcome will be analyzed using an ANCOVA, with continuous secondary outcomes analyzed using Poisson regression. Direct observations will be conducted of the implementation and application-specific training sessions provided to each site. Semi-structured interviews will be conducted with participants, healthcare providers, organizational leaders, and system stakeholders as part of the embedded process evaluation. Thematic analysis will be applied to the qualitative data in order to describe the relationships between (a) key contextual factors, (b) the mechanisms by which they effect the implementation of the intervention, and (c) the impact on the outcomes of the intervention, according to the principles of Realist Evaluation.

**Discussion:**

The use of mobile health and virtual tools is on the rise in health care, but the evidence of their effectiveness is mixed and their evaluation is often lacking key contextual data. Results from this study will provide much needed information about the clinical and cost-effectiveness of a mobile application to improve diabetes self-management. The process evaluation will provide valuable insight into the contextual factors that influence the application effectiveness, which will inform the potential for adoption and scale.

**Trial registration:**

Clinicaltrials.gov NCT02813343. Registered on 24 June 2016 (retrospectively registered).

Trial Sponsor: Ontario Telemedicine Network

## Background

E-Health solutions are increasingly common in healthcare, and involve the use of an electronic device or monitoring system by individuals or their healthcare providers to monitor or improve their health status [1]. Well-designed e-Health solutions for diabetes management targeting health behaviour change can improve a range of measures, including improvements in glycemic control, perceived health, and a reduction in hospitalizations [2, 3]. Furthermore, e-Health has been shown to streamline communication among providers and enable the provision of care by providing providers with improved knowledge, skills, and confidence [4]. Most notably, these solutions may provide an opportunity to improve access to enhanced care for marginalized populations and may be cost-effective to implement at scale.

An obvious area in which e-Health holds potential is the management of Type 2 Diabetes (T2DM). The global prevalence of diabetes continues to rise, with projections estimating 9 % of the population will be impacted by 2035 [5]. In Canada alone, over 2.4 million individuals are living with diabetes, with anticipated increase in prevalence to 3.7 million Canadians by 2018 [6]. Diabetes is the leading cause of adult blindness [7] and end stage renal disease among Canadians [8], with the cost of care for individuals with diabetes currently reaching 3–4 times that of those without the disease [6].

Management of diabetes through improvements in glycemic control [9] and risk factor modification can help prevent long-term complications [10]. Unfortunately, evidence-to-practice gaps are well documented in diabetes care [11]. In addition, much of the management of diabetes lies not in the hands of health care providers, but in the day-to-day self-management of the millions of people living with this chronic condition whose lives are complex and not solely defined by the disease. This reality drives the increasing interest in innovative strategies to improve self-management that emphasizes convenience and recognizes the realities of people’s busy lives. Although the use of mobile interventions to improve diabetes self-management significantly improved glycaemic control [12], substantially heterogeneity in intervention design and implementation continues to be a reality [3]. Among successful interventions, the most common behaviour change techniques include prompt self-monitoring and feedback on performance [3]- features that are easily incorporated as part of mobile technology.

In light of the evidence, health system decision makers in Ontario, Canada are interested in evaluating the effectiveness, implementation, and impact of mobile-based self-management tools for T2DM among diverse patient populations throughout the province. Lessons learned are likely to be useful across a wide variety of chronic conditions and therefore have significant potential to address the triple aim of improved population health outcomes, enhanced patient experience and reduced health care costs per capita. This pragmatic evaluation will explore not only whether the intervention produces an effect, but how and why this effect (or lack thereof) is produced.

The primary objective of this study is to evaluate whether a mobile application designed to improve self-management and experience of care can improve clinical outcomes compared to usual care for people with T2DM. The secondary objectives are to determine the effects on patient experience and health system costs; to evaluate how and why the intervention worked as observed; and to gain insight into considerations for system-wide scale-up. The inclusion of the embedded process evaluation within the overall study design presents a novel contribution in the e-Health literature by including a methodological approach to provide insight into how e-Health tools function more generally, beyond their application to diabetes care. The project evaluation is based on a model of integrated knowledge translation [13], whereby the health system decision makers, implementation leads, and scientific evaluators have collaborated to inform the development of the research project from the outset.

## Methods

We designed a pragmatic, randomized, wait-list-control trial with an embedded qualitative process evaluation to evaluate whether and how a mobile application designed to improve self-management and experience of care among patients with T2DM has an effect on clinical outcomes and healthcare utilization. The protocol received ethics approval from Research Ethics Boards at participating institutions, including Women’s College Hospital, St. Joseph’s Care Group, North York General Hospital, and William Osler Health System. The trial is registered on ClinicalTrials.gov (NLM Identifier: NCT02813343).

### Setting

Most health services in Ontario, Canada are financed through the publicly-funded Ontario Health Insurance Program (OHIP). OHIP covers medically necessary services provided by physicians, including primary care, emergency services, inpatient medical services, and specialist visits. In addition to OHIP, the Ministry of Health & Long-Term Care funds Diabetes Education Programs (DEPs), which are community-based, multi-disciplinary programs accessible through both physician and self-referral. DEPs provide diabetes education services for clients who are aged 18 or over. Their primary focus is the provision of diabetes education and management services for individuals diagnosed with diabetes or pre-diabetes according to the Canadian Diabetes Association Guidelines [14]. This includes education around self-monitoring blood glucose levels, screening for complications, nutrition, physical activity, and appropriate management strategies including vascular protection, and optimizing glycemic control.

Participating DEPs were selected by the Ontario Telemedicine Network (OTN) and include the Diabetes Health Centre in Thunder Bay, the Diabetes Education Center at North York General Hospital, and two Diabetes Education Centers belonging to the William Osler Health System. OTN reached out to the Provincial Chronic Disease Management-Local Health Integration Leads Council for help in identifying organizations who would be good partners in this initiative. These sites serve a socially and ethnically diverse range of patients with diabetes, representing more than 4500 Ontarians annually. Each site serves distinct populations, including a large aboriginal population in Thunder Bay and visible minorities and new immigrants in the William Osler Health System.

### Stakeholders

The intervention will be implemented by the OTN, a non-profit, government funded organization and the largest provider of telemedicine services in the province of Ontario [15]. OTN’s involvement in an advisory capacity increases the likelihood that the study results will have a future impact on health system policy. This engages the principles of integrated knowledge translation to collaboratively produce knowledge [16], with the aim of optimizing health care delivery and associated clinical outcomes. The study is funded by Canada Health Infoway.

### Trial design

The study is a pragmatic, randomized, wait-list-control trial with blinded outcome assessment. It is important to note that the study design reflects an external, third-party evaluation. The evaluation team is independent from both the application vendor and the implementation team, which is coordinated and controlled by OTN. A pragmatic randomized trial design was chosen because it is a methodology that guides the assessment of whether an intervention works when introduced into a public health or clinical setting (i.e., in real-life conditions). Participants are randomized into one of two groups: an immediate treatment group (ITG) and a wait-list-control (WLC) group. The ITG group immediately begins using the application (e-Health intervention), for a total duration of six months (refer to Fig. 1). The WLC group receives usual care for the first three months, at which point they will cross over to the intervention arm and use the application for a total of 3 months.

**Fig. 1 Fig1:**
[figure not shown]
Flow of Participants

#### Eligibility

Patients are eligible for inclusion into the study if they meet the following criteria: 1) adults over the age of 18; 2) obtaining care for T2DM at a participating DEP; 3) HbA1c ≥ 8.0 % (and at least 1 % above the participant’s target level) on most recent laboratory report within the last 3 months 4) currently using an active email address or able and willing to obtain one; and 5) able to read the English language (self-reported). Patients are excluded if they have Type 1 diabetes; are on continuous glucose monitoring; have an insulin pump; are on dialysis; are pregnant; or are unable to use a computer or mobile phone due to severe mental or physical impairment. The inclusion criteria are intentionally broad to align with the objectives of pragmatic trial design to determine whether the application works under usual conditions to promote generalizability [17]. The diagnostic exclusion criteria reflect a set of conditions in which there are distinct and unique self-management needs, which the application is not currently designed to address.

#### Recruitment

Participants are recruited from participating DEPs associated with three institutions across Ontario. A clinician at each site identifies potential eligible participants during their regularly scheduled clinical appointment. Interested individuals meet with a site coordinator who provides them with an information brochure and a consent form to review. Interested participants contact the research assistant using the dedicated study phone line. The research assistant obtains and documents verbal informed consent and collects baseline outcome measures (refer to Fig. 2, Part A). Participants are then randomized to one of the study arms. Following randomization, the site coordinator collects clinical information (refer to Fig. 2, Part B) and provides participants in the ITG with a study-specific mobile phone. Participants enter initial clinical information into the application (medications, etc.) while in clinic and the data is reviewed for accuracy by a clinician (nurse, nurse practitioner, or certified diabetes educator). Participants in the WLC group receive their application-enabled phone in person following completion of the control phase (three months after enrollment).

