#### Allocation

Randomization is centralized, web-based and generated by the Applied Health Research Centre (AHRC) at the Li Ka Shing Knowledge Institute of St. Michael’s Hospital. Randomization is stratified by site using randomly permuted blocks of varying sizes, which are not known by the study team.

Once the participant has been enrolled and the baseline assessments are completed, randomization occurs in REDCap™, a web-based electronic data entry system, where the participant is automatically assigned a group allocation (ITG or WLC).

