#### Data collection

Baseline information including demographics and health status will be collected using an electronic case report form (CRF) (refer to Fig. 2). HbA1c values will be recorded at baseline, 3 months, and 6 months. Participants who do not have a recent value within two weeks of the study assessment will be given a requisition to perform blood work during the first study visit. Baseline information will be collected by a research assistant via a telephone call, after which the participant will be formally enrolled in the study. Participants who fail to complete the baseline assessment will not be enrolled. Follow up data will be collected using a secure online questionnaire administered via REDCap™ that can be completed by participants from any device with an internet browser and connection (computer, tablet etc.). Weekly reminders will be sent to participants who fail to complete the questionnaire, with a maximum of three reminders. Participants who express a preference for phone communication will be contacted by the research assistant, following the same reminder protocol. Application utilization data is tracked directly through the application and will be extracted at the end of the study.

Healthcare utilization and cost outcome measures will be obtained from health administrative data available through the Institute for Clinical Evaluative Sciences (ICES). At the time of study enrolment, patients will be asked to provide consent to link their OHIP number to health administrative data. ICES is a non-profit research institute with a secure and expansive repository of Ontario’s health-related administrative data from hospital, physician, long term care and other related health services paid for by the provincial health insurance plan. These data are linked using encrypted identifiers. Data from this study will be linked to ICES data using encrypted health card identifiers created by ICES authorized personnel. ICES is a prescribed entity and data custodian under the Personal Health Information Protection Act (PHIPPA).

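### The stated sequence allows some baseline HbA1c values, the implied ANCOVA covariate, to be drawn after randomisation and possibly after the app is handed over

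*Protocol article*

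**What the plan says.** The Recruitment section of the protocol article gives an order of events. A research assistant takes verbal consent and collects the Part A baseline measures, the participant is randomised, and a site step follows: "Following randomization, the site coordinator collects clinical information (refer to Fig. 2, Part B) and provides participants in the ITG" with their phone. The next sentence covers app set-up: "Participants enter initial clinical information into the application (medications, etc.) while in clinic".

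The Data collection section schedules HbA1c at baseline, 3 months and 6 months. A participant with no value within two weeks of the study assessment "will be given a requisition to perform blood work during the first study visit". That visit is not defined, and no latest date for the draw is given. The same section describes the baseline information as gathered by telephone before formal enrolment, and bars from enrolment anyone who does not complete the baseline assessment.

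The Allocation section says: "Once the participant has been enrolled and the baseline assessments are completed, randomization occurs in REDCap". The Eligibility section accepts an HbA1c of at least 8.0% "on most recent laboratory report within the last 3 months".

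The Data analysis section specifies an ANCOVA at three months and names baseline HbA1c as covariate only for the 6-month comparison. The Power calculation section assumes a correlation of 0.80 between baseline and follow-up HbA1c, which implies the same covariate at three months.

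**The concern.** ANCOVA relies on a covariate that treatment cannot have touched. If some baseline HbA1c samples in the immediate treatment group are drawn after the app has begun to act, the adjustment treats early benefit as a baseline difference and removes part of it from the estimate. The trial is open to participants, so someone who already knows they are wait-listed may also be less inclined to go for the draw. Whether a baseline value exists could then depend on arm.

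The eligibility value may be up to three months old, while the baseline rule asks for one within two weeks of the study assessment. The requisition route may therefore be used often, although the article gives no share.

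**Working it through.** **1. Sequence.** These are the contacts described between first approach and follow-up.

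| Step | Mode | Relation to randomisation | Could blood be requisitioned here? |
|---|---|---|---|
| Site coordinator gives brochure and consent form | On site | Before (and before consent) | Not described |
| Consent and Part A baseline measures | Telephone | Before | Not described |
| Randomisation in REDCap | Web | n/a | n/a |
| Part B data, phone for the immediate group, app set-up | On site | After | Fits the first study visit |

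The only on-site contact described between consent and follow-up comes after randomisation. Data collection describes baseline information as a telephone collection, so the condition in Allocation can be met without a fresh HbA1c sample. The stated order thus permits a draw after randomisation but does not say that one happens.

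**2. The plan's power figure.** Inputs from the Power calculation section: difference 0.7, SD 2, correlation 0.80, alpha 0.05, and 300 × 0.85 = 255 analysed. Assumed: two-sided test and 1:1 allocation, so 127.5 per arm.

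- Residual SD = 2 × √(1 − 0.80²) = 1.2
- Standard error = 1.2 × √(2/127.5) = 0.150
- Power = Φ(0.7/0.150 − 1.96) = 0.9965 (0.9963 with the noncentral t), against 0.997 stated

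The figure is reproduced only with the baseline adjustment. Without a covariate, power is 0.798. This supports reading baseline HbA1c as the primary covariate.

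**3. Bias from late draws.** The ANCOVA estimate is the difference in follow-up means minus slope × the difference in baseline means. Let f be the share of the immediate group drawn after app start, and e the fall in HbA1c already achieved by then. The observed baseline mean in that group is lower by f × e, so

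bias toward zero = slope × f × e = 0.8 × f × e,

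with slope = 0.80 × (2/2) = 0.8 on equal SDs. The article gives neither f nor e, so the values below are assumptions. The last two columns come from a simulation of 4,000 runs per scenario.

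| f | e | Bias | Expected estimate | Power | Simulated estimate | Simulated power |
|---|---|---|---|---|---|---|
| any | 0 (same-day draw) | 0 | 0.70 | 0.9965 | 0.699 | 0.996 |
| 0.25 | 0.1 | 0.02 | 0.68 | 0.9948 | n/a | n/a |
| 0.5 | 0.1 | 0.04 | 0.66 | 0.9925 | 0.658 | 0.992 |
| 0.5 | 0.2 | 0.08 | 0.62 | 0.9848 | 0.622 | 0.987 |
| 1 | 0.2 | 0.16 | 0.54 | 0.9488 | 0.538 | 0.949 |
| 1 | 0.35 (extreme) | 0.28 | 0.42 | 0.798 | 0.422 | 0.802 |

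Relative to the planned effect, 0.02/0.7 is 3% and 0.16/0.7 is 23%. The last row needs every draw in the immediate group to be late and half the effect already achieved. It is shown only as a limit.

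**4. Missing baselines.** The article gives nothing from which to size arm-dependent missingness, so no figure is offered.

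**The case against.** The strongest reply is that no sentence places an HbA1c draw after randomisation. The first study visit is undefined, and the figures with participant flow and the case report form are not available here. The form might show HbA1c in Part A. Recruitment calls Part A baseline outcome measures and Part B clinical information, so the baseline assessments in Allocation may mean Part A alone, and the sections would then give one order. If HbA1c does belong to the baseline assessment, the rule that non-completers are not enrolled already provides the needed gate.

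This stands as far as it goes: the late draw is an inference. But the two defences pull apart. If baseline assessments means the telephone part only, nothing requires the HbA1c sample before allocation. If it includes HbA1c, a requisition handed out at a visit after randomisation contradicts it. Neither reading guarantees a pre-treatment covariate from the text as it stands.

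The reply is also right on size. Requisition and phone may be given at the same visit, and blood drawn that day carries essentially no treatment effect. The bias runs toward zero, so by itself it would not create a false positive.

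A reader might further infer that the wait-list group's 3-month sample could fall after its phone hand-over. The documents do not support that as a finding: the phone follows completion of the control phase, and the order of draw and hand-over within that visit is operational detail that an article may leave to the full protocol.

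**Conclusion.** The point holds as a sequencing fault. The article's own order permits a covariate measured after randomisation, and its sections need to be reconciled. A reader might conclude that baseline HbA1c is in fact collected after the app starts, or might attach one fixed percentage of lost effect by assuming a delay for every patient. The documents support neither, because they state no draw date, no delay and no share of patients needing a new sample.

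The plausible cost is an attenuation of 0.02 to 0.16 HbA1c points on a planned 0.7, with power staying at or above about 0.949. This rests on a slope of 0.8, late shares of 0.25 to 1, early changes of 0.1 to 0.2 points, and a late value that predicts follow-up as well as a true baseline would. What is at risk is an unbiased effect estimate and baseline data that are equally complete in both arms, rather than the trial's ability to detect the effect.

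**What to change.** Make the Recruitment, Allocation and Data collection sections agree. Issue the HbA1c requisition at consent, and have REDCap release the allocation only after the baseline sample is drawn and Part B is complete. Define the first study visit accordingly. The cost is protocol wording, one REDCap condition, and a few days' delay to randomisation for patients who need a new sample. Part B would have to be collected before the phone is handed out. With 14 participants recruited at publication, the change would cover 300 − 14 = 286 of the target.

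If that gate is not adopted, use the eligibility HbA1c, which is always measured before randomisation, as the covariate for all participants in both arms. Do not substitute it only where the draw was late: lateness arises after allocation and can differ by arm, so the definition of the covariate would too. The price is precision. A value up to three months old may correlate with follow-up at less than 0.80, and at the planned SD of 2 power would move from 0.9965 toward the unadjusted 0.798 as that correlation falls.
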